### Sample size calculation

2.2

In this study we have 9 outcomes. In the presence of several outcomes, sample size should be calculated for the outcome with the smallest difference in effect size before and after [40]. Chronic pain patients' pain is usually high, even 7 or higher, and pain often remain with no change in clinical treatment studies. Minimal cut-off change for pain has been detected in previous studies. Salaffi et al., 2004 [41] stated that minimal cut-off point measure of Numeric Rating Scale of NRS pain is −1.0 cm. When pain is 7.5 before intervention, and after intervention 6.5, the effect size is 13%. The difference in pain acceptance and fear-avoidance beliefs may even be larger than 15% pre- and post-intervention [41]. By using stepped wedge analysis on the study design matrix (6 groups with 4 observations of each group) and with 15% detectable minimum difference of the outcome (chronic pain, mean 7.14 in a scale from 0 to 10) we calculated the minimum group sample size to be 10 (when a-error is 0.05 and b-error 0.80) and total number of participants to be 60 [42].

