The content of the baseline and of the follow-up questionnaires is, to a large extent, the same. They contain the same 10 questions from the screening questionnaire, as well as questions on pain-related fear, pain self-efficacy, chronic pain acceptance, self-rated work ability, the number of sick-leave days due to any reason and due to pain, medication use for pain and for other purposes, non-pharmaceutical treatments in use, feeling energized, enjoying life, physical exercise, smoking, body weight and height, and chronic diseases. Sickness-absence data and use of occupational health services is collected from the OHS patient register 6 months before and 6 months after intervention.

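### Percentage change cannot identify the limiting outcome among nine, so the power claim is supported at most for pain intensity and is unsupported for the rest, including the two register counts

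*Protocol article*

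**What the plan says.** Section 2.2 (Sample size calculation) opens with "In this study we have 9 outcomes"; the Abstract calls all nine primary and ranks none. The section then gives the sizing rule: "In the presence of several outcomes, sample size should be calculated for the outcome with the smallest difference in effect size before and after".

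The rule is applied in three steps:

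- The minimal relevant change in pain is taken from a cited study: "minimal cut-off point measure of Numeric Rating Scale of NRS pain is −1.0 cm".
- That change is turned into a percentage of the pre-intervention value: "When pain is 7.5 before intervention, and after intervention 6.5, the effect size is 13" per cent.
- Two other outcomes are set beside it: "The difference in pain acceptance and fear-avoidance beliefs may even be larger than 15% pre- and post-intervention". The remaining six get no figure.

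The calculation is then done for pain: "By using stepped wedge analysis on the study design matrix (6 groups with 4 observations of each group"), a 15% difference on a mean of 7.14, alpha 0.05 and a b-error printed as 0.80. The result is 10 per group and 60 in total. No SD, intra-cluster correlation or within-person correlation is printed.

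For the two register outcomes, section 2.7 (Data collection) says: "Sickness-absence data and use of occupational health services is collected from the OHS patient register 6 months before and 6 months after intervention". Table 2 ties neither of them to any questionnaire occasion.

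**The concern.** The rule is meant to guarantee that a sample large enough for the hardest outcome is large enough for all. It works only if outcomes are ranked on the quantity that drives power, which is the expected difference divided by the SD. Percentage change from baseline contains no SD, and its size depends on which end of the scale is called zero. Table 2 mixes directions (pain: 10 is worst; work ability: 10 is best) and also includes a 0-7 day item and register counts, so the percentages are not on a common footing. This is a wrong criterion stated in the text, not a detail that an article may leave out.

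Absence days and service use are part of the stated aim, yet they are not in the comparison and do not have the four observations that the calculation uses. If the trial is taken to be sized for its least favourable outcome, a null result on either could be read as evidence of no effect when the design may have had little chance of detecting one.

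**Working it through.** **Inputs from the article.** Pain 7.5 to 6.5; minimal change 1.0; 15% of a mean of 7.14; 6 groups of 10; 4 observations per group; three groups start at once and three wait (section 2.4); one 6-month register window before and one after.

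**Assumptions.** Two-sided alpha; b-error 0.80 read as power 0.80; matrix 0111 for three groups and 0011 for three (Fig. 1 is not available); period effects in the model; ICC 0-0.10; within-person correlation 0, 0.5 or 0.7; no dropout. CVs (SD/mean) and the 15% target for the counts are also assumed.

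**1. The article's percentage, and its dependence on direction.**

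- As scored: (7.5 - 6.5)/7.5 = 13.3%.
- Scored as 10 minus pain: (3.5 - 2.5)/2.5 = 40%.
- The sizing target: 0.15 x 7.14 = 1.071 points. On the reversed scale this is 1.071/2.86 = 37.4%.

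The difference in points, the SD and the power are identical in both directions. Only the percentage moves, so it cannot rank outcomes for power.

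**2. What N = 60 implies for pain.** The SD at which 1.071 points has 80% power is 1.071/[(1.96 + 0.84) x s], where s is the standard error of the treatment effect for an SD of 1, from generalised least squares on the 6 x 4 matrix.

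| Within-person correlation | SD for 80% power | Detectable difference in SD units (1.071/SD) |
|---|---|---|
| 0 | 1.38-1.48 | 0.78-0.72 |
| 0.5 | 1.87-1.93 | 0.57-0.55 |
| 0.7 | 2.38-2.48 | 0.45-0.43 |

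Cross-check: a plain 30 v 30 comparison detects 2.80 x sqrt(2/30) = 0.72 SD, giving SD = 1.071/0.72 = about 1.48. This agrees with the first row at ICC 0. The stated N can be right for pain under some SDs and correlations and wrong under others. With none printed, it can be neither reproduced nor refuted.

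**3. The same design applied to a count with a 15% change.** The standardised effect is 0.15/CV. Power is Phi(0.15/(CV x s) - 1.96), with s over the range used in step 2.

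- CV 0.5 (effect 0.30 SD): 19-50%.
- CV 1.0 (effect 0.15 SD): 8-16%.

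**4. The two values that the register outcomes actually have.** Paired t-test, n = 60, noncentrality sqrt(60) x (0.15/CV)/sqrt(2(1 - r)). This flatters the design, since it has no control for time and no losses.

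| Pre-post correlation r | CV 0.5 | CV 1.0 |
|---|---|---|
| 0.3 | 49% | 16% |
| 0.5 | 63% | 21% |
| 0.7 | 84% | 31% |

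For scale, pure Poisson variation at an assumed mean of 5 contacts gives CV = 1/sqrt(5) = 0.45; overdispersion would raise it.

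**The case against.** **Pain was not chosen by percentage alone.** Section 2.2 also says that pain often does not change in treatment studies, and section 2.10 says that other interventions have not moved VAS significantly. Low expected responsiveness is a legitimate reason to suspect that pain is limiting. It stands as a rationale, but it does not supply the SDs that a ranking needs and says nothing about the register counts.

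**The percentage does not visibly damage N.** The calculation uses an absolute difference of 1.071 points, which reversing the scale would not change, and an SD may have been entered in the software and not printed. This also stands: N = 60 for pain is unverifiable, not shown wrong. An unreported SD would not repair the selection step, which is done in percentages in the text.

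**The article is modest elsewhere.** It plans exact confidence intervals (section 2.11), calls the sample rather small (section 4), and says that ethics, finance and workable group size also shaped N (section 2.3). It nowhere says outright that 80% power holds for each outcome. That coverage is the implication of the rule in section 2.2, not a separate claim.

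**Power for the register counts.** A reader might infer that 80% power fails for absence days and contacts, or is far below 80%. The article does not support that. The 15% is borrowed from pain, and no mean, SD or target effect is given for either count. At CV 0.5 and correlation 0.7 the paired comparison reaches 84%. A 30% reduction at CV 1.0 has the same standardised effect as 15% at CV 0.5, so it too would give 49-84%.

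**Conclusion.** The point holds in limited form. Percentage change from the pre-intervention value is the wrong criterion for choosing the limiting outcome. It contains no SD, it turns 13% into 40% when the scale is reversed, and it is reported for three of nine outcomes. It cannot establish that pain is limiting or that N = 60 serves all nine. The 6 x 4 matrix also does not describe the two register outcomes, which have two values per person.

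The 80% power is therefore unsupported for outcomes other than pain. For the register counts it is probably low if they are overdispersed: 8-31% across both analyses at CV 1.0 and 19-84% at CV 0.5, all for an assumed 15% change and the assumed matrix and correlations. Failure is not demonstrated, and nothing here shows that N = 60 is wrong for pain. The matter should be corrected, but it does not threaten the design.

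**What to change.** In section 2.2, delete the ranking by percentage change. State that the power calculation applies to pain intensity only, giving the difference in points and the SD and within-person correlation used, and print 0.80 as power if that is what is meant. State that no power is claimed for the other outcomes.

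If a limiting outcome is still wanted, rank outcomes by expected difference divided by SD.

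For the other outcomes, give the detectable standardised difference at N = 60, using two values rather than four for the register outcomes, and report them as estimates with confidence intervals. Standardised units are the practical choice because section 2.3 says there are no pilot data to supply SDs for each outcome.

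Do not change N. The cost is a rewording and a short table, with no extra participants or data. The downside is a narrower power claim.

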### Randomization

2.3

Occupational health nurses, doctors, and psychologists and physiotherapists are responsible for recruiting 60 mainly Finnish study participants and know well the participants’ medical history and with the participants go through all inclusion and exclusion criteria. Meta-analysis by Bernardy et al., in 2010 involved whether CBT has any effect on fibromyalgia symptoms. The median number of patients with CBT was 40, with group size ranging from 7 to 64. Of the 527 patients in the CBT groups, 81% and in the control groups 75% completed therapy [20]. Consistently, we estimate those, who will take part in our study as ranging from 75% to 81%. Choice of the final sample size is influenced also by its being unethical to have a large sample if the benefit of treatment is unknown. Final sample size is also influenced by the adequacy of financial resources. We will ask for voluntary group leaders among its personnel: psychologists, nurses, and physicians. Moreover, we will recruit one pain nurse from the hospital pain clinic. Three tutor pairs comprise group leaders. In each patient group will be 10 participants, the recommended group size (8–10 participants) for the tutor to be able to work with every participant during the 2-h meeting. Six groups with 10 participants each is estimated to provide sufficient data for the statistical analyses, with no pilot study data.

Since this intervention includes pain psychotherapy (CBT, mindfulness, attendance, and commitment therapy ACT) with topics about chronic pain differing in every meeting, including homework, increasing the sample size to account for dropout is not recommendable. With increasing sample size, new participants would not take part in all group meetings, which could weaken peer support and reliability and the validity of research results. Subjects who fulfill the inclusion criteria (Table 1) and express an interest in participating in the study will be individually interviewed ([name], [name]). In this interview, inclusion and exclusion criteria will be topics asked about, in person. All will be informed about the study, and provide their written informed consent including their participation as being voluntary. They will receive information stating that during the study, each subject is able to use occupational health services as before. During the recruitment phase, the subjects fill out the short screening questionnaire (Scr), the modified Örebro questionnaire.

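### Section 2.2 misprints its power as a type II error of 0.80 and sizes on 1.07 points although its own minimal pain change is 1.0 point; the power left after the expected loss is not stated

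*Protocol article*

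**What the plan says.** Section 2.2 (Sample size calculation) sets a rule for a trial with nine outcomes: "sample size should be calculated for the outcome with the smallest difference in effect size before and after". For pain it takes a minimal cut-off change of 1.0 from a cited study and works it through: "When pain is 7.5 before intervention, and after intervention 6.5, the effect size is 13" per cent. Of two other outcomes it says: "The difference in pain acceptance and fear-avoidance beliefs may even be larger than 15% pre- and post-intervention". The calculation itself is for pain, on six groups with four observations each, with a "15% detectable minimum difference of the outcome (chronic pain, mean 7.14 in a scale from 0 to 10". The result is "we calculated the minimum group sample size to be 10 (when a-error is 0.05 and b-error 0.80", giving 60 in total.

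Section 2.3 (Randomization) takes completion rates of 81% (treated) and 75% (control) from a meta-analysis and applies them here: "we estimate those, who will take part in our study as ranging from 75% to 81" per cent. It then says that "increasing the sample size to account for dropout is not recommendable", because later entrants would miss meetings and peer support could suffer. It also cites ethics and finances as limits on the sample.

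**The concern.** Three statements do not fit together.

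- **The error rate.** Power is one minus the type II error, so "when a-error is 0.05 and b-error 0.80" describes a trial that would miss a true effect four times in five. Nobody plans that, but it is what is printed.
- **The difference.** The section names 1.0 point as the smallest change that matters for pain and then sizes on a larger one, while still calling it the minimum. Raising the target difference lowers the required number.
- **The number of people.** Ten per group is presented as the minimum that achieves the power, and the next section expects a fifth to a quarter not to complete. Declining to inflate is a legitimate choice, but the power claim then no longer describes the expected trial.

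The stake is how a null result for pain would be read. A reader would take it as coming from a trial with 80% power for the minimal change, which the plan's own figures do not support.

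**Working it through.** **Inputs.** From Section 2.2: alpha 0.05 (taken as two-sided; the article does not say), mean pain 7.14, detectable difference 15%, minimal change 1.0 point, 10 per group, 60 in total. From Section 2.3: participation 75–81%. Assumed: the intended power is 0.80. No SD, planning intra-cluster correlation or design matrix is visible (Fig. 1 is not shown).

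**1. The plan's own figures.**
- 6 × 10 = 60. This agrees.
- 0.15 × 7.14 = 1.071 points.
- 1.0/7.5 = 13.3%, the plan's 13%. On the mean actually used, 1.0/7.14 = 14.0%.
- So the sizing difference exceeds the minimal change by 0.071 points, a ratio of 1.071.

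**2. Can 10 per group be reproduced?** Not from the article. Solving a standard stepped-wedge variance (cluster random effect, fixed periods) for the SD that makes 10 per group give 80% power at 1.071 points, with an intra-cluster correlation of 0 to 0.2, gives about 1.4–1.5 for one plausible six-by-four matrix. Two others give about 1.7–2.1. The figure is neither confirmed nor refuted. The steps below therefore take the plan's claim as given and only rescale it; they need no SD.

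**3. Power for 1.0 point.** At 80% power the standardised effect is 1.960 + 0.842 = 2.802. It scales with the difference and, approximately, with the square root of the fraction giving data: power = Φ(2.802 × (difference/1.071) × √fraction − 1.960).

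| Giving data | Power, 1.071 points | Power, 1.0 point |
|---|---|---|
| 60 (100%) | 80% | Φ(2.616 − 1.960) = 74% |
| 48.6 (81%) | Φ(2.522 − 1.960) = 71% | Φ(2.355 − 1.960) = 65% |
| 45 (75%) | Φ(2.427 − 1.960) = 68% | Φ(2.266 − 1.960) = 62% |

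**4. Difference detectable with 80% power.** 1.071/√0.81 = 1.19 points and 1.071/√0.75 = 1.24 points, or 16.7–17.3% of 7.14.

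**5. How soft these values are.** Ten is the smallest whole number that suffices, so power at 10 could exceed 80%. If 9 per group just fell short and variance is inversely proportional to group size, the standardised effect is at most 2.802 × √(10/9) = 2.954. This gives up to 84% at 1.071 points. For 1.0 point the ranges become 74–79% with 60, 65–70% at 81% and 62–67% at 75%. The detectable difference could be as low as 1.071 × √(9/10) = 1.016, divided by √0.81 or √0.75, which is 1.13 or 1.17 points.

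**The case against.** **The sizing rule concerns which outcome to use.** The plan did size on pain, the outcome it presents as changing little, so the rule was followed in that respect. This stands. What remains is that the change used for pain is larger than the minimal change given for pain a few lines earlier. Rounding 14.0% up to 15% would be no defence, since it makes the required sample smaller. The gap is modest: 0.071 points, about 6 percentage points of power.

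**The 15% belongs to other outcomes.** A reader might infer that the percentage was borrowed from pain acceptance and fear-avoidance. The text says only that their differences may exceed 15%; it does not assign them that value.

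**The trial has only 20% power.** A reader might infer this from the printed error rate. It is almost certainly a label slip, and correcting it changes no number if 80% power was meant.

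**Dropout was ignored.** The documents do not support this. Section 2.3 states the expected participation, considers inflation and declines it with reasons. Only the silence on what that does to power is open to criticism.

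**The 45–49 figure is a worst case.** The 75–81% comes from therapy completion elsewhere, and Section 2.11 (Statistical analysis) plans intention-to-treat mixed models, which can use partial data. This largely stands. Against it, Section 2.5 (Timetable) collects the post-intervention and 6-month questionnaires at group meetings, so leaving the group may well mean losing those measurements.

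**The sample is openly called small.** Section 4 (Limitation) says so, but its example is generalisability, not power.

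**Conclusion.** The point holds in two parts on the page and in one narrower part. The type II error is printed wrongly, and pain is sized on 1.071 points against a stated minimal change of 1.0. The power claim is also not restated for the participation the plan itself expects.

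The size is moderate. Instead of 80%, power for the minimal change is about 74% with all 60. With 45–49 giving data it is roughly 62–65%, when about 1.2 points would be detectable with 80% power. These values assume that 80% power was meant, that 10 per group gives just that at 1.071 points, and that non-completers give no data. Relaxing the last two assumptions raises them.

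It would go too far to conclude that 10 per group is wrong. Some plausible combinations of SD, intra-cluster correlation and matrix do yield it. The absence of those inputs from a condensed article is not itself the fault.

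**What to change.** Keep 60 participants and the decision not to inflate. In Section 2.2:

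- Replace the error-rate wording with power 0.80 (type II error 0.20), if that was meant.
- Reconcile the 13% and 15%: state power for the 1.0-point change, or say why 1.071 points is the target.
- Using the authors' own SD, intra-cluster correlation and design matrix, report power for 1.0 point with all 60 and with the expected 45–49, and the difference then detectable with 80% power. The values above show the likely order of size; they are not text for the protocol.
- Say that ten per group is the number that can be run in a group, with the power that follows, instead of a minimum that assumes full retention.

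The cost is one recalculation and a reworded paragraph, with no change to design, numbers or analysis. The downside is a less favourable power statement.

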### Randomization

2.3

Occupational health nurses, doctors, and psychologists and physiotherapists are responsible for recruiting 60 mainly Finnish study participants and know well the participants’ medical history and with the participants go through all inclusion and exclusion criteria. Meta-analysis by Bernardy et al., in 2010 involved whether CBT has any effect on fibromyalgia symptoms. The median number of patients with CBT was 40, with group size ranging from 7 to 64. Of the 527 patients in the CBT groups, 81% and in the control groups 75% completed therapy [20]. Consistently, we estimate those, who will take part in our study as ranging from 75% to 81%. Choice of the final sample size is influenced also by its being unethical to have a large sample if the benefit of treatment is unknown. Final sample size is also influenced by the adequacy of financial resources. We will ask for voluntary group leaders among its personnel: psychologists, nurses, and physicians. Moreover, we will recruit one pain nurse from the hospital pain clinic. Three tutor pairs comprise group leaders. In each patient group will be 10 participants, the recommended group size (8–10 participants) for the tutor to be able to work with every participant during the 2-h meeting. Six groups with 10 participants each is estimated to provide sufficient data for the statistical analyses, with no pilot study data.

Since this intervention includes pain psychotherapy (CBT, mindfulness, attendance, and commitment therapy ACT) with topics about chronic pain differing in every meeting, including homework, increasing the sample size to account for dropout is not recommendable. With increasing sample size, new participants would not take part in all group meetings, which could weaken peer support and reliability and the validity of research results. Subjects who fulfill the inclusion criteria (Table 1) and express an interest in participating in the study will be individually interviewed ([name], [name]). In this interview, inclusion and exclusion criteria will be topics asked about, in person. All will be informed about the study, and provide their written informed consent including their participation as being voluntary. They will receive information stating that during the study, each subject is able to use occupational health services as before. During the recruitment phase, the subjects fill out the short screening questionnaire (Scr), the modified Örebro questionnaire.

**Table 1 tbl1:** Condensed outline of meeting content.

	
First meeting:	• Tutor introduction, goals, rules, practical issues • Participant introduction in pairs, brief description of the symptoms of pain, current work ability, motivation to participate, expectations • Discussion on pain management tools already in use • Homework: “Foreword, *A New Understanding of Pain, My Story*” (pages 1–39) in book Rethinking pain
Second meeting:	• Short Relaxation/Mindfulness Practice before every meeting • Theme of the meeting: new knowledge on pain, mechanisms, differences between acute and chronic pain, individuality of pain, reality of pain, role of the brain and central nervous system • Discussion on pain mechanisms • Discussion about homework Homework: “Fostering Sleep” (pp.54–61), “Doing What You Enjoy” (pp.80–102), “Be Aware of Presence” (pp.142–149), “Yoga” (pp.194–198) in book Rethinking pain
Third meeting:	• Themes of the meeting: sleep, mindfulness, meditation, yoga • Group work on 1. Doing pleasurable things will help improve pain management 2. How pain affects social life, and vice versa • Discussion of homework Homework: “Work” (pp.150–161) and Appendices 2 (pp.232–233), and 3 (pp.234–241), link to www.otakipuhaltuun.fi, link for awareness exercise for Orton's pain patient (duration: 10 min, by psychologist [name]) https://www.youtube.com/watch?v=xczkxCdNYmQ
Fourth meeting:	• Theme of the meeting: work • Pair discussion: The importance of work in life. Objectives of work. Professional development. The future of working life. Supervisors and co-workers - hopes and expectations directed towards supervisors and co-workers. On sick leave or at work despite pain. What can be done at work to improve work ability. Pairs present their thoughts. Group discussion follows • Discussion of homework Homework: “Develop Positivity” (pp.62–71), “Touch and Be Touched” (pp.72-29), “Talk about Your Emotions” (pp.103–112), “Love” (pp.162–169), “Get a Pet” (pp.170–177)
Fifth meeting:	• Themes of the meeting: emotions, love, touch, sexuality, nurturing a positive attitude, having a pet • Discussion of homework Homework: “Nourish Yourself” (pp.113–127), “Exercise With Joy” (pp.128–141), “Manage Your Weight” (pp.178–187), “Quit Smoking” (pp.188–193), “Cultural Power” (pp.205–214) + Appendix 1 (p.230): “Things You Can Affect And How They Affect pain”.
Sixth meeting:	• Themes of the meeting: new tools to improve pain management, making one's pain management plan • Filling out the follow-up inquiry • Discussion of homework and pain management tools. • Homework: The pain management plan will be given for writing at home
Seventh meeting, 6-month follow-up, Eighth meeting 12-month follow-up for ABC groups	• Themes of the meeting: psychological flexibility, importance of training and awareness skills, work as rehabilitation • Updating the pain management plan

Both participants and interviewers are blinded for the randomization, and at the end of the interview participants are randomized to one of the six groups (A, B, C, D, E, F). In this stepped-wedge design, every participant knows that he or she will receive an intervention, and the researchers know that no one will be left without treatment, which is not the case in conventional RCT [43].

The request for pain-management group activity originates with the patients themselves. Occupational Health Helsinki has provided three other kinds of groups during the previous 5 years (groups for sleep problems, depression, and burnout). The practical framework for our pain-management group is based on the feedback from those groups (size, facilities, timing, length, language, visual tools). After discussion between the leadership of the city of Helsinki and Occupational Health Helsinki, the results of this study will be provided to the participants in the form of the result report (via e-mail) as well as articles in the media (OHC website, Twitter and such).

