# The effect of pain management group on chronic pain and pain related co-morbidities and symptoms. A stepped-wedge cluster randomized controlled trial. A study protocol

**DOI:** 10.1016/j.conctc.2020.100577

**Published:** 2020-06-18

**Keywords:** Pain management, Chronic pain, Self-efficacy, Health services, Occupational health

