### Study design

2.4

This study is a randomized controlled trial with a stepped-wedge design, where all clusters and participants in clusters receive intervention eventually in random order [43] (Fig. 1). Participants are randomized to either a group starting intervention within 1–3 weeks after the recruitment, or to a waiting-list group. The waiting-list group starts the intervention after the first group has completed the intervention, i.e., after approximately 4 months. Three groups (A, B, C) with 10 subjects each start the intervention immediately, and three groups (D, E, F) with 10 subjects each are on the waiting list.

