**Fig. 1 fig1:**
[figure not shown]
Study design of a stepped-wedge cluster randomized controlled trial. Shaded cells are intervention periods, and blank cells are control periods. This trial has six data-collection points. Surveys: Scr = screening, Bef1 = before intervention (1st time), Bef2 = before intervention (2nd time), Aft = immediately after intervention, Aft6m = 6 months after intervention, Aft12 m = 12 months after intervention, for only half of the clusters.

The participants’ own OH nurses and doctors are informed about the study and are responsible for the participants' medical care as usual, if needed. The researchers ([name], [name]) are not involved in treating the study participants during the study, to prevent any influence on the results. No restrictions exist in initiating or changing the pain medication or other treatment modalities or examinations during the study.

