### Statistical analysis

2.11

The post-intervention period is compared with the pre-intervention (control) period. Linear mixed-effect models allow analysis of repeated measures data and the differences in the outcomes of interest between intervention and control periods. Intention-to-treat analyses are conducted, and time-effect and intra-cluster correlation coefficients reported. When the null hypothesis (i.e., no difference) is rejected, it is always possible to conclude, whatever the results of the study are, that there exists a difference but actually there is not (type-I error or false positive) [51]. Since the sample size is rather small, exact confidence interval for outcomes will be the choice to avoid statistical bias and false-positive or false-negative errors [51].

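### Participants are randomised individually, yet the trial is labelled, sized and partly analysed as cluster randomised; the unit must be reconciled, group correlation tied to treated periods, and the exact interval defined

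*Protocol article*

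**What the plan says.** Two statements in the protocol article make the person the unit of randomisation. Section 2.3 (Randomization): "at the end of the interview participants are randomized to one of the six groups (A, B, C, D, E, F"). Section 2.4 (Study design): "Participants are randomized to either a group starting intervention within 1–3 weeks after the recruitment, or to a waiting-list group".

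Other statements make the group the unit. The title reads "A stepped-wedge cluster randomized controlled trial". Section 2.4 says that "all clusters and participants in clusters receive intervention eventually in random order". The Fig. 1 legend reads "Study design of a stepped-wedge cluster randomized controlled trial".

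The label carries into the numbers and the analysis:
- Section 2.2 (Sample size calculation) derives 10 per group and 60 in total: "By using stepped wedge analysis on the study design matrix (6 groups with 4 observations of each group").
- Section 2.4 gives two start times: "Three groups (A, B, C) with 10 subjects each start the intervention immediately", and D, E and F wait about 4 months.
- Section 2.11 (Statistical analysis) names linear mixed-effect models, says that intra-cluster correlation coefficients will be reported, and adds that "exact confidence interval for outcomes will be the choice to avoid statistical bias and false-positive or false-negative errors".

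Section 2.11 does not give the exact method or its unit, and it does not give the random effects.

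**The concern.** No clinic, workplace or other existing cluster is named anywhere. The six groups come into being through the allocation of individuals. What sections 2.3 and 2.4 describe is an individually randomised comparison of immediate and delayed group treatment.

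The difference has consequences. In a cluster trial, members share something before and after the switch, and a group effect that is constant over control and treated periods is a usual starting point. Here the members of D, E and F share nothing until they meet. Section 2.5 has their two pre-intervention questionnaires sent by mail, the second one handed in on the first meeting day. Correlation from shared sessions and tutors can start only with the meetings. A constant cluster effect misplaces it, and an ICC pooled over all periods would describe neither period.

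The promise of an exact interval needs a unit as well. If exactness comes from the randomisation, someone must say what was randomised, and that is where the article contradicts itself. An exact interval controls coverage under its own assumptions; it does not remove bias or false negatives, as section 2.11 suggests.

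**Working it through.** **1. The plan's own figure.** Section 2.2 gives a difference of 15% of 7.14 = 1.071 points, alpha 0.05 (taken as two-sided) and power 0.80 (printed as a b-error). No SD or ICC is given, so 10 per group can be neither confirmed nor refuted. With four observations per group, the matrix is 0111 for A–C and 0011 for D–F. Only the second column contains both treated and untreated groups. At ICC 0 the standard stepped-wedge (Hussey–Hughes) power then equals that of 30 v 30 at that visit:

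power = Φ(1.071 / (SD × √(2/30)) − 1.96)

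- SD 1.48: 1.071 / 0.382 − 1.96 = 0.84, power 0.80.
- SD 1.5: 1.071 / 0.387 − 1.96 = 0.81, power 0.79.

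Over ICC 0 to 0.2, 10 per group gives 80% power on this matrix only if the SD is about 1.38 to 1.48. These SDs are implied values, not documented ones.

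**2. What an exact interval could mean.**

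| Unit permuted | Allocations | Smallest two-sided p |
|---|---|---|
| Six groups, 3 v 3 | C(6,3) = 20 | 2/20 = 0.10 |
| Individuals, 30 v 30 | C(60,30) = 1.18 × 10^17 | about 1.7 × 10^−17 |

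With groups as the unit, a two-sided 95% interval obtained by inverting the test is unbounded (the one-sided floor is 1/20 = 0.05). With individuals there is no practical limit.

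**3. Why treated-period correlation matters: a hand check.** Compare the arms at one visit, with only the treated arm clustered in groups of 10. The true standard error exceeds the naive one by √((1 + (1 + 9 × ICC)) / 2):
- ICC 0.05: √((1 + 1.45)/2) = 1.107. The naive 5% test rejects at 2 × (1 − Φ(1.96/1.107)) = 7.7%.
- ICC 0.10: √((1 + 1.90)/2) = 1.204, giving 10.4%.

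The article does not plan this single-visit analysis. It only shows the mechanism.

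**4. Mixed models under no treatment effect.** Null simulation, 500 runs per scenario, assumed within-person correlation 0.6, group effect active only when treated:

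| Random effects | ICC 0.05 | ICC 0.10 |
|---|---|---|
| Participant only | 7.4% | 9.2% |
| Participant + constant cluster | 7.8% | 9.6% |
| Participant + treated-period group | 5.8% | 6.0% |

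The last model's standard error is about 10 to 16% larger. The Monte Carlo error near 5% is √(0.05 × 0.95 / 500) = about 1 percentage point. The first two rows therefore exceed 5% by more than two such errors, while the third does not differ clearly from 5%.

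**The case against.** **The model is not fixed in the article.** Section 2.11 states no random-effect structure, and a condensed article may leave that to the SAP. This stands: the rejection rates apply to models that the stated label invites, not to a model that the article commits to. The contradictory unit and the undefined exact interval are printed in the article, so that allowance does not cover them.

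**The exact floor.** A reader might infer that six clusters make 5% significance impossible for every outcome. The documents do not support that. Section 2.11 never says that groups are permuted, its named model has no such floor, and the people actually randomised provide ample permutations.

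**Intervals far too wide.** A reader might also infer this from a model with a cluster intercept and no participant effect. Section 2.11 presents mixed models as the means of handling repeated measures, so that model is not a fair reading of the plan.

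**Exact mixed-model intervals can exist.** In some balanced designs they do. Section 2.3 expects only 75% to 81% participation, so balance cannot be counted on. The fair criticism is that the term is undefined.

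**The rates rest on assumptions.** The article gives neither the ICC nor the within-person correlation. Shorter null runs of the participant-only model at ICC 0.05 scattered, from 4.5% (400 runs) to 8% (300 runs). The direction agrees with the hand check; the decimals should not be relied on.

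**The sizing.** No error in the number 60 is shown, because its inputs are missing.

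**Conclusion.** The concern holds in a limited form. The article contradicts itself on the unit of randomisation: by its own description the trial is individually randomised, and the cluster label states a property that it does not have. This does not weaken the randomisation. It does leave open which correlation structure the analysis should carry and which unit an exact interval would use.

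The size is moderate and conditional. At an assumed within-person correlation of 0.6 and treated-period ICC of 0.05 to 0.10, a constant-cluster or participant-only mixed model has a type I error of about 7 to 10% instead of 5%, against about 6% for a group effect active only when treated. If the treated-period ICC is close to zero, the difference is negligible. The two-sided floor of 0.10 applies only if the exact method permutes the six groups.

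**What to change.** 1. In the title, abstract, section 2.4 and Fig. 1, describe the trial as individually randomised to immediate or delayed group treatment, and say in section 2.2 how the six-group calculation relates to that design.
2. In section 2.11, specify a participant random intercept plus a group random effect that is active from that group's first meeting, with small-sample degrees of freedom (for example Kenward–Roger).
3. Replace the exact confidence interval with that model's interval, or with a re-randomisation interval that permutes individuals under the allocation rule actually used. The latter is exact against no effect of any kind on any participant; it does not by itself carry variation between groups, so say which question is meant.
4. Report the ICC for treated periods only.

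The cost is wording and a slightly different model, with no new data. Under the assumptions above, the standard error grows by roughly 10 to 16%. The group variance rests on six groups and will be imprecise. Section 2.3 also has three tutor pairs leading six groups; the simulation did not include correlation through shared tutors, so the plan should say how it is handled.
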